### Procedure

The methodological guidelines established by Elliott-Sale *et al*^27^ for research in sports and exercise sciences with female participants will be followed to conduct the study. In addition, the recommendations proposed by Schmalenberger *et al*^28^ and Janse de Jonge *et al* for studying the MC will also be considered.^29^

#### Familiarisation, MC monitoring and determination of MC phases

For this study, three out of the widely considered four phases of the MC will be selected: phase 1 (EFP), when oestrogen and progesterone are at their lowest blood concentrations; phase 2 (late follicular phase: LFP), when the highest oestrogen concentration occurs while progesterone remains low; and phase 4 (mid-luteal phase: MLP), the highest concentration of progesterone and a high concentration of oestrogen occur (figure 2). These phases will be identified following the protocols proposed by Peinado *et al*^20^ and Janse de Jonge *et al*.^29^

**Figure 2 F2:**
[figure not shown]
A depiction of a 28-day menstrual cycle with ovulation on day 14, showing the typical fluctuations in ovarian hormones, such as oestrogen, progesterone and luteinising hormone (LH), as well as the changes in temperature, during the follicular and luteal phases. Modified from Peinado *et al*^20^ and Schmalenberger *et al.*^28^ Timing of sessions for an average duration cycle (28 days): from the first day of bleeding, the tests will be performed between the first and fifth day (EFP=low levels of sex hormones), between days 11 and 13 (LH peak or the same day; LFP=low levels of progesterone but high oestrogen levels), and between days 19 and 23 (after ovulation; MLP=elevated levels of both progesterone and oestrogen). EFP, early follicular phase; LFP, late follicular phase; MLP, mid-luteal phase.

During the 2–3 months before the intervention, familiarisation with the tests and PA sessions will be conducted. This familiarisation period will start with MC monitoring, allowing the appointment setting for/in each MC phase with little margin of error. For the monitoring of the MC and the setting of the appointments, the experimental considerations described below will be followed^27 29^:

Monitoring will be carried out starting 3 months before starting the intervention. Participants will be requested to provide information regarding the starting date of their six previous menstruations to estimate their MC duration. Then, during the two to three subsequent MCs, period starting dates will be collected concurrently with the familiarisation stage.Luteinising hormone (LH) peak detection urine kits will detect LH surge, ovulation, and, retrospectively, the LFP. This test will allow us to confirm that the MCs included in the study are ovulatory, as anovulatory cycles can occur even in normal cycles with regular menstruation.^29^In addition, serum hormone concentrations (see Reproductive hormonal profile subsection) will be measured for each training session retrospectively since this is a direct method and is considered the gold standard for research purposes.

Therefore, a three-step method will be used for MC phase confirmation, combining the calendar method, qualitative determination of LH peak in urine and analysis of serum hormones, following the protocols described by Peinado *et al*^20^ and Janse de Jonge *et al*.^29^ After the familiarisation period, a posteriori exclusion of participants and/or cycles who/which do not fulfil the levels of oestrogen and/or progesterone concentrations expected for each phase will be applied.

Additionally, familiarisation sessions will be conducted, employing the exercises used in the HIIT and strength training sessions, and these sessions will also be used to estimate the 1-RM (repetition maximum) and maximal oxygen consumption (VO_2_max) of each participant.

#### Randomisation

In this crossover study, the evaluation order will be counterbalanced according to the MC phases (EFP, LFP and MLP) using codes 1–3. Participants and their counterparts will undergo evaluations in different sequences: 1–2–3; 2–3–1; 3–1–2; 2–1–3; and 1–3–2.^20^ Additionally, the type of exercise (HIIT: 1 or strength training: 2) they will perform in each phase will be randomised. This randomisation approach will ensure an equitable distribution of the effects of the MC and the types of exercise among participants, contributing to obtaining more robust and reliable results for the analysis. The ‘OxMaR’ software will be used for the participant randomisation process.^30^

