Thus, the objectives of the study are: (a) to identify moderating variables that modify satisfaction with HIIT and strength training sessions throughout the MC in females with and without MS, and (b) to compare the acute effects of different types of PA sessions (HIIT and strength training) throughout the MC, in females with and without MS.

The central hypotheses of this study are the following: first, during the luteal phase of the MC, females with MS are expected to show a stronger association between inflammation and perception (fatigue and energy) and hormonal levels, as compared with females without the disease. Furthermore, HIIT and strength training sessions are expected to impact satisfaction with PA practice in both populations throughout the MC. During the luteal phase of the MC, females with MS are expected to exhibit different acute responses to HIIT and strength training sessions as compared with females without the disease.

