## Material and methods

### Design

The present protocol describes the methodology of the EMMA Study, a randomised, single-blind crossover trial conducted on females with MS, matched 1:1 based on age, lifestyle factors (smoking, PA) and country of residence, with females without MS, to analyse the effect of PA practice (HIIT vs strength training) throughout the MC. To achieve this, the Consolidated Standards of Reporting Trials recommendations and protocols^19^ and previous studies that analysed the impact of the MC in females without MS^20^ will be followed. Participants will visit the facilities approximately 10 times (4 preliminary familiarisation visits and 6 visits to carry out HIIT and strength training session in each phase of the MC) over 3–4 months (figure 1).

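### Phase order is described as counterbalanced, but only five of the six possible orders are listed, so phase and session position are not balanced

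*Protocol article*

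**What the plan says.** The Randomisation section states that "the evaluation order will be counterbalanced according to the MC phases (EFP, LFP and MLP) using codes 1–3". It then gives the list: "Participants and their counterparts will undergo evaluations in different sequences: 1–2–3; 2–3–1; 3–1–2; 2–1–3; and 1–3–2". Exercise type is handled separately: "the type of exercise (HIIT: 1 or strength training: 2) they will perform in each phase will be randomised". The section concludes: "This randomisation approach will ensure an equitable distribution of the effects of the MC and the types of exercise among participants".

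The Design section gives six exercise visits per woman, described as "6 visits to carry out HIIT and strength training session in each phase of the MC". No allocation ratio across the five orders is stated, and nothing explains why 3-2-1 is left out. Objective (b), at the end of the Introduction, is to compare acute effects of the two session types across the cycle in women with and without MS.

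**The concern.** Counterbalancing means that each phase falls equally often in each position, so that anything that changes from one session to the next does not load onto a particular phase. With one of six orders missing, this property is lost.

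The women have had no structured exercise programme in the past 6 months (exclusion criterion d). Satisfaction, fatigue, soreness and strength could change with repeated sessions through habituation, learning or a smaller reaction after the first bout. If they do, part of that change would appear as a phase difference in any comparison that ignores position. At stake are the comparisons between phases under objective (b) and the accuracy of a stated design property.

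**Working it through.** **Inputs.** The five orders and the codes 1 = EFP, 2 = LFP, 3 = MLP come from the Randomisation section; the coding is read from the order in which the phases are named there. Equal allocation over the five orders is assumed. Position means place within one pass through the three phases. Randomising exercise type does not change the order of phases.

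**Step 1: position of each phase in each order.**

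| Order | EFP | LFP | MLP | MLP minus EFP |
|---|---|---|---|---|
| 1-2-3 | 1 | 2 | 3 | +2 |
| 2-3-1 | 3 | 1 | 2 | -1 |
| 3-1-2 | 2 | 3 | 1 | -1 |
| 2-1-3 | 2 | 1 | 3 | +1 |
| 1-3-2 | 1 | 3 | 2 | +1 |
| Mean | 9/5 = 1.8 | 10/5 = 2.0 | 11/5 = 2.2 | 2/5 = +0.4 |

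Counts in first/second/third place are EFP 2/2/1, LFP 2/1/2 and MLP 1/2/2. MLP follows EFP in 3 of 5 orders and precedes it in 2 of 5.

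**Step 2: transitions.** 1-2, 2-3, 3-1 and 1-3 occur twice each; 2-1 and 3-2 occur once each.

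**Step 3: can another ratio restore balance?** Position balance needs each phase in each place with weight 1/3. MLP is first only in 3-1-2, EFP is last only in 2-3-1, and LFP is second only in 1-2-3. Each of these orders must therefore carry 1/3. They sum to 1, which leaves 0 for 2-1-3 and 1-3-2. No allocation that uses all five orders is balanced for position.

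**Step 4: size of the possible bias.** With a linear period effect of delta per position and no adjustment:
- MLP-EFP: (2.2 - 1.8) x delta = 0.4 x delta.
- MLP-LFP: (2.2 - 2.0) x delta = 0.2 x delta.

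The documents give no value for delta, so the result stays in units of delta.

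**Step 5: the group comparison.** If the period effect is delta_MS in one group and delta_C in the other, with the same sequence weights, the group difference in the MLP-EFP contrast is biased by 0.4 x (delta_MS - delta_C). This is 0 when the two are equal.

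**Step 6: if period is fitted.** In a model with additive subject, period and phase effects and equal allocation, all phase contrasts are estimable and unbiased by additive drift. The variance of each pairwise phase contrast, in units of sigma squared/n, is 2.083 with the five orders and 2.00 with all six. Efficiency is 2.00/2.083 = 96%.

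**Step 7: all six orders.** Adding 3-2-1 gives each phase 2/2/2 over the three places, a mean position of 2.0 for each, and two of every transition.

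**Step 8: is 3-2-1 too long?** The mid-window days for a 28-day cycle in the Figure 2 legend are 3, 12 and 21.
- 3-2-1: days 21, 28 + 12 = 40 and 56 + 3 = 59; span 38 days.
- 2-1-3: days 12, 28 + 3 = 31 and 28 + 21 = 49; span 37 days.
- 1-3-2: days 3, 21 and 28 + 12 = 40; span 37 days.

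The missing order takes about one day more than two orders already in use.

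**The case against.** The strongest reply is that the omission does little harm, and much of that reply stands.

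- **The luteal hypotheses are between groups.** The Introduction says "During the luteal phase of the MC, females with MS are expected to exhibit different acute responses to HIIT and strength training sessions"; the reference there is the group of women who do not have MS. Both groups draw on the same list of orders, so a common period effect cancels. A reader might infer that these hypotheses are themselves biased. The document does not support that without period effects or sequence weights that differ by group.
- **The bias needs an unadjusted analysis.** The article shows no model, and that choice can properly be left to the analysis plan. Fitting period removes additive drift.
- **Delta may be small.** The protocol has four familiarisation visits and uses the session exercises in familiarisation, so the first study session is not first exposure. The primary outcomes also have pre-session values, so a drift in level alone drops out of pre-to-post change.
- **Carry-over is weakly motivated.** The Figure 2 windows (days 1-5, 11-13 and 19-23) are at least 6 days apart within a cycle, while follow-up after a session ends at 72 hours.

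Two further readings are tempting and go too far. One is that the luteal phase is always tested later. It is later than EFP in 3 of 5 orders, and even that average rests on equal allocation. The other is that matched partners are given different orders, adding order effects to the MS comparison. The sentence can equally mean that pairs are spread over the list with both members sharing an order. Separate randomisation of partners would in any case add variance, not a directional bias.

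What the reply does not touch is the stated property. The listed scheme is not counterbalanced, and a period term in the model would not make the description true.

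**Conclusion.** The point holds as a design flaw of moderate weight that should be fixed. That the five listed orders cannot balance position is certain and does not depend on the allocation ratio. The direction and size (MLP on average 0.4 positions later than EFP, hence 0.4 x delta) rest on three assumptions: equal allocation, a linear period effect, and a within-group phase contrast that ignores position. If period is fitted, the cost falls to about 4% of efficiency, assuming additive effects. The between-group luteal hypotheses are largely protected.

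**What to change.** Before the first allocation, add 3-2-1 to the list, allocate the six orders equally, and fit session position (period) as a fixed effect. At 30 per group this gives 30/6 = 5 women per order. At the stated minimum of 15 per group, 15/6 = 2.5, so the split is slightly uneven. Position balance can still be kept with 3 women on each of 1-2-3, 2-3-1 and 3-1-2 and 2 on each of the other three (9 + 6 = 15), because each set of three puts every phase once in every place. Transitions would then occur 6 or 4 times each.

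The cost is a revised randomisation list and, for women on 3-2-1, a span about one day longer than the longest order now listed.

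If the five orders are kept, fit period, accept the loss of about 4% in efficiency, state the allocation ratio, and remove the claims of counterbalance and equitable distribution. In either case, one added sentence should say whether the two members of a matched pair share an order.

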The inclusion criteria will be as follows: (a) women aged between 18 and 40 years old; (b) females with an MC length of ≥21 days and ≤35 days of natural menstruation; (c) absence of iron deficiency anaemia (serum ferritin >20 µg/L, haemoglobin >115 µg/L and transferrin saturation >16%); (d) being in a stable phase of the disease; and (e) to ambulate autonomously for more than 100 m. Participants will be excluded if they have: (a) a score <2 or >6 on the Expanded Disability Status Scale; (b) experienced a relapse in the 12 months before enrolment; (c) received corticosteroid treatment in the previous 2 months; (d) participated in a structured exercise programme in the past 6 months; (e) secondary amenorrhoea (absence of ≥3 consecutive periods despite not being pregnant and having previous menstruation); (f) used or currently using hormonal contraceptives for 3 months before recruitment; (g) reported musculoskeletal or neurological injuries not associated with MS, recent surgical interventions or pregnancies in the previous year; (h) diseases unrelated to MS. Furthermore, exercise and dietary restrictions and recommendations will be established 24 hours before the sessions, on the intervention day, and 24, 48 and 72 hours after, following the recommendations outlined in Peinado *et al*.^20^ Participants will be instructed not to modify their lifestyle during their participation in the project.

In addition to these inclusion and exclusion criteria, participants will be required to provide information, following the recommendations of Elliott-Sale *et al*,^27^ pertaining to the number of pregnancies (single or multiple pregnancies); age at menarche and any complications; previous MC irregularities; contraceptive use in the 12 months before the study, specifying the type (implants, injections, intrauterine devices/hormonal intrauterine systems, vaginal rings, transdermal patches) and formulation; the number of pregnancies resulting in gestational age of 24 weeks or more, regardless of whether the child was born alive or stillborn. Additionally, data on habitual PA (International Physical Activity Questionnaire), daily caffeine intake, dietary intake and nutritional supplements, alcohol consumption and smoking will be collected. Participants will also be asked to indicate the date of their MS diagnosis and the number of relapses.

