#### Experimental procedures

All sessions will be conducted at the same time of day to avoid different responses to changes in circadian rhythm, and the temperature (21–22°C) and humidity (45–60%) of the evaluation areas will be controlled. In the first visit, fasting (4 hours) and resting without exercising in the previous 24 hours will be required. First, participants will be informed about the study’s objectives, sign the informed consent forms, complete the health and lifestyle questionnaires, and the inclusion and exclusion criteria will be assessed. Subsequently, descriptive data will be collected, and body composition and anthropometric tests will be performed. Finally, blood samples will be collected. Second and third visits will be performed to familiarise the participants with the maximal ramp test on a cycle ergometer and 1-RM exercise to individualise the physical exercise sessions and to familiarise them with the different tests. Subsequent visits will be scheduled according to the timing of the MC phases estimated in the monitoring months. A pre-intervention, immediate post-intervention, 24, 48 and 72-hour post-intervention assessment will be performed at each MC phase (hormone profile). A HITT and strength training session will be performed between the pre-assignment and post-assignment. Table 1 shows the activities to be performed in each MC. This procedure will be performed twice (HIIT and strength training sessions). All outcomes will be assessed by study staff blinded to group assignments as far as possible.

**Table 1 T1:** Study activities

Outcomes	Baseline measurements in each cycle (1 time/cycle)	Baseline measurements in each phase of the MC (3 times/cycle)	Pre-sessions	Post-sessions	24 hours post-sessions	48 hours post-sessions	72 hours post-sessions
Primary outcomes							
Satisfaction			x	x	x	x	x
Visual Analogue Scale for Fatigue (VAS-F)			x	x	x	x	x
Secondary outcomes							
Abdominal obesity and anthropometric variables	x						
Dietary and nutritional monitoring	x						
Monitoring of PA levels	x						
Walking endurance (2-MWT)	x						
Physical self-perception		x					
Catastrophizing Pain Scale		x					
Modified Fatigue Impact Scale		x					
Multiple Sclerosis Quality of Life-54		x					
State anxiety and trait anxiety		x					
Body temperature		x					
Bioimpedance analysis		x					
Reproductive hormonal profile			x				
Inflammatory profiles			x	x*			
Cognitive profiles			x	x*			

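### The stated randomisation does not ensure balance: HIIT/strength order is only randomised, and the phase list omits one of the six orders

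*Protocol article*

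**What the plan says.** The Randomisation section treats two factors differently. For the phases, "the evaluation order will be counterbalanced according to the MC phases (EFP, LFP and MLP) using codes 1–3", and women and their counterparts "will undergo evaluations in different sequences: 1–2–3; 2–3–1; 3–1–2; 2–1–3; and 1–3–2". For the exercise, "the type of exercise (HIIT: 1 or strength training: 2) they will perform in each phase will be randomised". The section then concludes: "This randomisation approach will ensure an equitable distribution of the effects of the MC and the types of exercise among participants". It names the program to be used ("software will be used for the participant randomisation process") but gives no settings for it, and it neither states nor rules out blocks, strata or another restriction on the exercise draw.

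The Design section plans "6 visits to carry out HIIT and strength training session in each phase of the MC", and Experimental procedures confirms that the procedure is done once with each type. Every woman therefore does HIIT and strength training in all three phases. What the exercise randomisation can decide is the order of the two types.

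The group size is 15 in the Abstract and 30 in the Participants section, so both are used below.

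**The concern.** The section promises a result, and the promise has two parts. For exercise type, randomising an order does not make the HIIT-first and strength-first counts equal in groups this small. For phase, the word *counterbalanced* implies that each phase falls equally often in each position, and the printed list does not do that.

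Order could matter here. The Participants section excludes women who have "participated in a structured exercise programme in the past 6 months", and fatigue, pain and strength are followed to 72 hours after each session, so a change from first to second session is plausible. If such a change exists and HIIT comes first more often than strength in some phase and group, part of it appears in the unadjusted HIIT minus strength difference there. Objective (b) compares session types across phases in women with and without MS. Imbalance that varies by phase and group could therefore resemble the pattern being sought. The mid-luteal phase, which the hypotheses single out, is also the one that the printed list puts first least often.

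**Working it through.** The article gives no figure for balance of order, so there is nothing to reproduce. The checks use the five printed sequences, two types per phase, and n = 15 or 30 per group.

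**1. Chance imbalance in exercise order.** Assume simple 1:1 randomisation of type order. For one phase in one group:

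- n = 15, 10:5 or worse: 2 × P(Bin(15, 0.5) ≤ 5) = 0.302
- n = 30, 20:10 or worse: 2 × P(Bin(30, 0.5) ≤ 10) = 0.099

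The chance that at least one cell is this uneven depends on how many independent draws there are:

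| Draws | n = 15 | n = 30 |
|---|---|---|
| 6 (each phase and group separately) | 1 − (1 − 0.302)^6 = 0.88 | 1 − (1 − 0.099)^6 = 0.46 |
| 3 (matched pairs share an order) | 1 − (1 − 0.302)^3 = 0.66 | 1 − (1 − 0.099)^3 = 0.27 |

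**2. What an imbalance does.** Let τ be the true HIIT minus strength difference and d the second-minus-first session change. A HIIT-first woman shows τ − d and a strength-first woman τ + d. The unadjusted mean is τ + d × (strength-first − HIIT-first)/n. At 10:5 this is τ + d × (5 − 10)/15 = τ − d/3.

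Under simple randomisation the shift has mean 0 and SD d/√n, which is 0.258d at n = 15 and 0.183d at n = 30. With order balanced within each phase it is at most d/15 = 0.067d at n = 15 (8:7) and 0 at n = 30 (15:15).

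**3. Effect on the test.** The size of d is not in the documents. It was set at 0.5 and 1.0 SD of the within-woman difference, and the unadjusted paired test was simulated with no true difference (100,000 runs):

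| n | d (SD) | Rejection, all runs | Rejection, given a 2:1 or worse split |
|---|---|---|---|
| 15 | 0.5 | 5.1% | 8.7% |
| 15 | 1.0 | 5.1% | 13.7% |
| 30 | 0.5 | 5.0% | 13.4% |
| 30 | 1.0 | 5.0% | 25.9% |

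The mean estimate was 0 to within 0.002 SD. Adjusting for order removes the shift. At a 2:1 split this multiplies the variance by 1/(1 − (1/3)²) = 1.125.

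**4. The phase list.** Counting positions in the five printed orders:

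| Phase | First | Second | Third | Mean position |
|---|---|---|---|---|
| EFP (1) | 2 | 2 | 1 | 9/5 = 1.8 |
| LFP (2) | 2 | 1 | 2 | 10/5 = 2.0 |
| MLP (3) | 1 | 2 | 2 | 11/5 = 2.2 |

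If the five orders are used equally, 15 women give first-position counts of 6, 6 and 3. A linear trend of δ per position then shifts the unadjusted MLP minus EFP difference by (2.2 − 1.8)δ = 0.4δ, at any sample size. With 3–2–1 added, every phase appears twice in every position.

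**The case against.** A reader might infer that order effects bias the HIIT–strength contrast. The documents do not support that. The contrast is within-woman, randomised order leaves it unbiased on average, and type I error stays at about 5%. The distortion arises only given an uneven split, and a model with an order term removes it. That term belongs to an analysis plan that is not shown, so its absence here is no fault.

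Further objections have weight:

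- **Simple randomisation is assumed.** Block and stratum details are commonly left to a full protocol. If the software balances type order within phase and group, the probabilities above fall. The figure of 0.88 also needs six independent draws, which the article does not establish. If one draw fixes a woman's order for all phases, the imbalance is the same in each phase and does not mimic a phase-by-type effect.
- **Familiarisation may shrink the order effect.** The Design section plans four familiarisation visits, and the familiarisation section uses the same exercises as the sessions. Nothing shows that this removes the effect, but it cannot simply be presumed large.
- **The conclusion has a milder reading.** Each woman does three sessions of each type, so total exposure to the types is equal by design. On that reading the sentence is true for exercise type, but it comes from the crossover and not from the randomisation that the sentence credits.
- **The missing sequence may be a slip in the article.** If so, restoring it to the text settles that half of the point.

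What remains is that the section claims a guarantee, and neither its unrestricted wording on exercise order nor its five-sequence list supplies one.

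**Conclusion.** The point holds as an overstated claim and an avoidable weakness, not as a demonstrated bias in the exercise contrast. Under simple randomisation, a 2:1 or worse split in a given phase and group has probability 0.30 at n = 15 and 0.10 at n = 30. Such a split moves the unadjusted HIIT–strength difference by one third of a session-order effect of unknown size. The phase-list imbalance rests on no assumption about the draw: one of the six orders is absent from the printed list. Its consequence for MLP versus EFP (0.4 of any per-position trend) assumes equal use of the five orders and no adjustment for position.

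**What to change.** Replace the two-part scheme with one allocation list per group: all six phase orders, each crossed with HIIT-first and strength-first (12 rows). Assign women to rows at random.

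- **15 per group:** use the 12 rows once, plus 1–2–3, 2–3–1 and 3–1–2 with one or two of these three HIIT-first. HIIT is first in 6 + 1 = 7 or 6 + 2 = 8 women in every phase, and each phase takes each position 4 + 1 = 5 times.
- **30 per group:** use the 12 rows twice, plus each phase order once more with three of the six HIIT-first. HIIT is first in 12 + 3 = 15 women, and each phase takes each position 8 + 2 = 10 times.

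If type order is to vary between phases within a woman, keep the same balance in each phase. Say whether a woman and her matched counterpart share a row. Include session order in the model, because dropout (25% is allowed for) and exclusion of cycles after the hormone results can undo balance set at allocation. Do not cross type order with the present five-sequence list, which would carry its imbalance forward.

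If the scheme is kept, remove *will ensure* and *counterbalanced* from the section.

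The cost is a new allocation list, with no extra visits or participants. Order 3–2–1 should not lengthen the schedule noticeably: with the midpoints of the article's 28-day windows (days 3, 12 and 21), one pass takes 19 + 19 = 38 days, against 19 + 18 = 37 for 2–1–3 and 18 + 19 = 37 for 1–3–2, which are already listed.
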